**7.4 Safety**

### 7.4.1 Physical and neurologic examination

Physical examinations include examination of the general appearance, skin, neck (including thyroid), eyes (except for fundus examination), ears, nose, throat, lung, heart, abdomen, back, lymph nodes, and limbs. Neurological examinations include cranial nerves, limb movements and sensory functions, deep key streaks, Babinski reflexes, Chaddock signs, and cerebellar function tests.

**7.4.2 Height, weight, vital signs**

- Height: Evaluate only at screening. Measure in centimeters (cm).
- Weight: Weighs up to 0.1 kilograms (kg) with naked robes and shoes on each visit.
- Vital sign:

After resting for 5 minutes, use a mechanical sphygmomanometer to measure pulse, systolic and diastolic blood pressure in sitting position.

## 7.4.3 Adverse events

An adverse event means the appearance or aggravation of any undesirable signs, symptoms, or medical conditions that occur after obtaining the subject consent, regardless of the test drug relevance. Medical conditions / illnesses that existed prior to obtaining the subject consent are considered adverse events only if they have deteriorated since the start of the study. Abnormal laboratory performance figures and test results are adverse events only if they cause clinical signs or symptoms, cause the test drug to stop, or require treatment.

The occurrence of adverse events should be investigated by questioning each subject at each visit during the clinical trial. Adverse events may also be identified by voluntary reporting by the subject during visits or during visits, or by physical examination, laboratory testing, or other evaluation. For all adverse events, record the following information in the Adverse Events section of the CRF:

1. Severity (mild, moderate, severe)

2. Causal relationship with test drug (estimated / unspecified)

3. Duration (start date and end date, or duration of last test)

4. Is it a serious adverse events (SAE)

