**4.3 Secondary objective**

- To evaluate the change from baseline to week 24 of the following parameters in the two groups of patients with Alzheimer’s disease associated with and without white matter changes after rivastigmine patch therapy

- - MMSE (Mini-Mental State Examination)
  - Frontal Assessment Battery (FAB)
  - Alzheimer’s Disease Cooperative Study - Activities of Daily Living (ADCS-ADL)
  - Caregiver-Administered Neuropsychiatric Inventory (CGA-NPI)
  - Clinical Dementia Rating Scale-Sum of Boxes (CDR-SB)
  - Caregiver burden scale – Korean version of mini- Zarit
  - Adverse events

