**5. 4 Inclusion criteria**

1. Age range : 50 – 90 years of age
2. Sex distribution: both men and women. Females of non-childbearing potential or post-menopausal for at least 2 years
3. AD in NINCDS-ADRDA criteria, mild to moderate
4. probable AD with or without mild to moderate whiter matter lesions, excluding multiple large vessel infarcts or a single, strategically placed infarct (angular gyrus, thalamus, basal forebrain, territory of the posterior or anterior cerebral artery) on MRI scan (within 12 months)
5. MMSE score : 10 to 24 at screening
6. Hachinski scores ≤ 4
7. No clinically significant laboratory abnormalities, such as thyroid disease, vitamine B12 deficiency or folic acid deficiency

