### 6.2.3 Controlling medication doses and suspending doses

If the subject is unable to tolerate the assigned dose, dose adjustment and suspension of dosing are allowed. The following treatment coordination schemes are recommended:

• In the case of a tolerability problem, the caregiver contacts the researcher as soon as possible.

• If the tolerability problem improves and subsequent days of treatment are less than 3 days, resume treatment to the same dose level as before administration. At this time, if tolerability is still a problem and the subject receives a patch of 5 cm², the subject may be dropped from the test. If tolerability is still a concern and the subject is treated with a 10 cm² patch, resume treatment at the lower dose level.

• If the tolerability problem improves and the days of consecutive administration are more than three days, resume treatment at a lower dose than before administration.

• If the subject's tolerability has improved, restart the dose titration schedule. If the tolerability problem is caused again at the next dose titration step, administration may be omitted again. Future attempts to titrate the dose will be at the discretion of the investigator (ie, if necessary for tolerance, the dosage does not necessarily have to be titrated to the target maximum dose).

• The dose level reduction required due to tolerability issues is permissible at any time during the treatment period.

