# 7 Study visit and assessment

We described all study visits schedule and assessment activities in table 1.

The subject will be present on all scheduled visits within 7 days from the specified date or 7 days prior to the specified date within 14 days. Subjects who have been dropped early in the test after the baseline for any reason will re-arrange their visit as soon as possible to perform all assessments scheduled at the final visit.

**Screening visit:** Subject / guardian consent, demographic and background information, inclusion and exclusion criteria, NINCDS-ADRDA 'probable' diagnostic criteria for Alzheimer's disease, current / past history, concurrent medication, vital signs, physical examination, height, weight, neurological examination, MMSE, and the screening confirmation.

**Baseline visit:** This visit will be conducted within 28 days of the screening visit.

The baseline assessment included concomitant medication, dose regimens, compliance, ADAS-cog, MMSE, FAB ADCS-ADL, CGA-NPI, CDR-SB, Mini-Zarit, vital sign, physical examination, .

**Treatment visits:** A safety assessment is carried out at each visit. Safety assessments include signs of vital signs, physical examination, weight, neurological examination, and adverse events. Therapeutic evaluations are performed at each visit and include concurrent medications, dose-related records. The efficacy assessment was performed at the end of 24 weeks and included ADAS-cog, MMSE, FAB, ADCS-ADL, CGA-NPI, CDR-SB and Mini-Zarit. Subjects who discontinue treatment early will be assessed at the end of treatment at the end of the 24th week.

**Unscheduled visits**: Perform an assessment related to the cause of the unscheduled visit.

Table 1. Study Process

| **Assessment and activities** | **Visit schedule** | | | | |
| --- | --- | --- | --- | --- | --- |
| **Visit 1** | **Visit 2** | **Visit 3** | **Visit 4** | **Visit 5** |
|  | **D-28~1** | **Day 0** | 4wk****7d | 12wk****7d | 24wk****7d, or  Early termination |
| Informed consent | X |  |  |  |  |
| Inclusion/Exclusion criteria | X |  |  |  |  |
| Medical history | X |  |  |  |  |
| NINCDS/ADRDA probable AD criteria | X |  |  |  |  |
| **Concomitant Medication** | | | | | |
| Concomitant medication | X | X | X | X | X |
| Drug dosage description | X | X |  | X |  |
| **Efficacy measure s** | | | | | |
| ADAS-cog (patient) |  | X |  |  | X |
| Caregiver burden(caregiver) |  | X |  |  | X |
| MMSE(patient) |  | X |  |  | X |

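### Section 7.4.3 seeks adverse events by questioning patients with dementia and does not require the caregiver to be asked, so non-serious events are likely to be under-counted

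*Protocol*

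**What the plan says.** Section 7.4.3 sets the routine method: "The occurrence of adverse events should be investigated by questioning each subject at each visit during the clinical trial". It then names further sources, in a list that ends with a catch-all for any further assessment: "Adverse events may also be identified by voluntary reporting by the subject during visits or during visits, or by physical examination, laboratory testing". The caregiver appears in neither sentence. The same section defines an adverse event without regard to relation to the study drug, and asks for severity, causal relationship and duration of each event.

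The people questioned are defined by Section 5.4: "MMSE score : 10 to 24 at screening". Table 1 in Section 7 places adverse event assessment at Day 0 and at weeks 4, 12 and 24.

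The caregiver has a role elsewhere. Section 6.2.3 says: "In the case of a tolerability problem, the caregiver contacts the researcher as soon as possible". Table 1 uses the caregiver as informant for ADCS-ADL, CGA-NPI and caregiver burden at baseline and week 24.

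Section 4.3 ends its list of parameters for the two groups with "Adverse events". The analysis section on the secondary objective names the secondary outcomes without adverse events, and then describes their monitoring as a safety evaluation.

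**The concern.** The person asked to remember, date and grade events has, by the entry criteria, impaired cognition. The person best placed to help already serves as informant for other measures, but is not asked at the visit. The word subject cannot easily be read as covering the pair, because Table 1 labels instruments as patient or caregiver and Section 6.2.3 names the caregiver separately.

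At stake is how complete the record of milder events is. An incomplete record makes the treatment look better tolerated than it is in both groups. It also leaves less information for describing adverse events by white matter status.

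**Working it through.** **The plan's own figures.** The protocol states no adverse event rate, capture rate or power for adverse events, so there is no figure to reproduce. Its one design calculation (81 + 162 = 243, for ADAS-cog) reproduces if 80% power is assumed, and it has no bearing on this point.

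**Recall intervals (Table 1).**
- Day 0 to week 4: 4 weeks.
- Week 4 to week 12: 12 − 4 = 8 weeks.
- Week 12 to week 24: 24 − 12 = 12 weeks.

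The two longer intervals cover 8 + 12 = 20 of 24 treatment weeks (83%), including all scheduled time on the larger patch. If the printed 7-day window means a week either side, the last interval could reach 12 + 1 + 1 = 14 weeks.

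**Do the other sources fill the gap?**

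| Source | What it covers | What it leaves open |
|---|---|---|
| Caregiver contact (6.2.3) | Tolerability problems, promptly and between visits | Depends on the caregiver volunteering; narrower than the definition in 7.4.3; no link to the adverse event section of the CRF |
| Unscheduled visits (Section 7) | "Perform an assessment related to the cause of the unscheduled visit" | Someone must first raise the problem |
| Continuous monitoring (7.4.3, 7.5) | Serious events | Non-serious events |
| Examinations | Signs visible on the day | Table 1 has physical examination at Visits 1 and 5 only, while the text of Section 7 has it at every treatment visit |
| Laboratory testing | Named as a possible source in 7.4.3 | Not scheduled in Table 1 |

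On Table 1, adverse event questioning is the only safety item at Visit 3 (week 4), the visit from which the larger patch is scheduled. What remains open is the non-serious event that has resolved by the visit, that the patient does not recall and that the caregiver did not report.

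**Illustration of size. All rates and capture fractions are assumptions.** Observed rate = true rate × fraction captured, with the same fraction in both groups.

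| True rate | 90% captured | 70% captured | 50% captured |
|---|---|---|---|
| 20% | 18% | 14% | 10% |
| 40% | 36% | 28% | 20% |
| 60% | 54% | 42% | 30% |

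Where the true rates are equal, the observed rates stay equal. Where they differ, the difference shrinks. Take true rates of 40% without and 55% with white matter change, with the planned 200 and 100 patients, no dropout and a two-sided 5% test:

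power = Φ[(d − 1.96 × SE0) / SE1], where d is the difference in observed rates, SE0 = √[p̄(1 − p̄)(1/200 + 1/100)], SE1 = √[p1(1 − p1)/200 + p2(1 − p2)/100], and p̄ is the pooled rate.

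- Full capture: 40% v 55%, d = 0.150, p̄ = 0.45, SE0 = 0.0609, SE1 = 0.0606; power 0.69.
- 90% capture: 36% v 49.5%; power 0.61.
- 70% capture: 28% v 38.5%, d = 0.105, p̄ = 0.315, SE0 = 0.0569, SE1 = 0.0581; power 0.46.
- 50% capture: 20% v 27.5%; power 0.32.

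From full to 70% capture, power falls from 0.80 to 0.61 for true rates of 20% v 35%, and from 0.74 to 0.41 for 60% v 75%.

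**The case against.** The strongest reply is that the caregiver is not shut out. Section 6.2.3 has the caregiver call promptly, between visits, about the events most relevant to the drug, and that call is the first step of the dose-adjustment scheme. Serious events are monitored continuously, unscheduled visits are provided for, and Section 7.4.3 admits examination and other evaluation. This stands. A reader should not infer that caregivers have no reporting route, or that dose adjustment rests on patients' recall at visits. It limits the likely loss to non-serious events that the caregiver does not volunteer. It does not remove that loss.

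A reader might also infer that recall is worse in the white matter group, so that a false tolerability difference would appear. The protocol does not support this. Both groups have the same questioning, visit schedule and MMSE entry range, and any figure for such a bias would come entirely from recall rates chosen by the person computing it.

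Nor should the role of adverse events be overstated. Section 4.3 lists them for evaluation in the two groups, but the outcomes that Section 4.1 names for comparison do not include them, the analysis section treats them as safety, and no hypothesis is stated for them. The power figures above therefore show lost information, not a failed planned test.

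Finally, under-counting is an inference, since no capture rate is given. That is so, and it is why the conclusion is worded as likely.

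**Conclusion.** The point holds in a limited form. As written, Section 7.4.3 makes the patient the routine informant over intervals of 4, 8 and 12 weeks and does not require the caregiver to be questioned. Non-serious events not volunteered by the caregiver are likely to be under-counted, so event rates would be understated and the description by group weakened.

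This rests on two things: patients with MMSE 10 to 24 recalling such intervals incompletely, and caregivers not volunteering every event. The extent is unknown. Over assumed capture of 90% to 50%, a true 40% would be recorded as 36% to 20%. The protocol gives no ground for claiming bias between the groups, and the primary ADAS-cog comparison is not affected. It is a worthwhile, cheap improvement to safety data collection.

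**What to change.** Amend Section 7.4.3 in three respects:

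1. Name the caregiver beside the subject in the questioning sentence, for example: *At every visit, both the subject and the caregiver are asked about adverse events.*
2. Accept voluntary reports from either person.
3. State that caregiver contacts under Section 6.2.3 are entered in the adverse event section of the CRF, so that the two sections agree.

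The change alters no dose, visit or treatment rule. It costs a few minutes per visit. Caregiver scales are scheduled only at baseline and week 24, so a brief call may be needed if the caregiver is absent at week 4 or week 12. The reported event rate will probably rise, which should be expected when the results are set beside studies that asked patients only.

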**A serious adverse events (SAE) is defined as:**

• Lethal or life-threatening

• Continuous or significant disability / impairment of function

• Congenital defects or birth defects

• In a medical emergency, i.e. when the subject is at risk or needs medical or surgical intervention to prevent the consequences described above.

• Admission is not considered a serious adverse event if hospitalization or extension of existing hospitalization is required, such as:

- Common treatments not related to disease worsening

- Selective and pre-planned treatment of existing disease that is not related to the indications of this trial and has not deteriorated since the beginning of the study drug

- Emergency outpatient treatment that does not fall within the definition of serious adverse events described above and does not result in hospitalization

- Societal reasons and deterioration of general condition of the patient are not accompanied by short-term hospital admission

Unlike routine safety assessments, critical adverse events are continuously monitored and reported in accordance with specific reporting procedures (see section 7.5).

All adverse events should be treated appropriately. Such treatment may include one or more of the following measures: no action taken (i.e., continuous observation), test drug dose adjustment / intermittent discontinuation; Permanent discontinuation of the test drug due to the adverse event; Concomitant drug administration; Enforcement of non-medication laws; Subject Admission / Extension of the period of stay for the subject. Record the action taken to treat the adverse event in the Adverse Event section of the CRF.

If an adverse reaction is found, follow-up should be done until the adverse event is resolved or determined to be permanent, and the change in severity at each visit, its relevance to the test drug.

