## 7.5 Report of serious adverse events

To ensure patient safety, every SAE, regardless of suspected causality, occurring after the patient signs the informed consent and until 4 weeks after the patient has stopped study treatment must be reported to Novartis Safety Desk within 15 days of learning of its occurrence. Any SAEs experienced after this 4-week period should only be reported to Novartis Safety Desk if the investigator suspects a causal relationship to the study drug.

Recurrent episodes, complications, or progression of the initial SAE must be reported as follow-up to the original episode within 15 days of the investigator receiving the follow-up information. An SAE occurring at a different time interval or otherwise considered completely unrelated to a previously reported one should be reported separately as a new event.

Information about all SAEs is collected and recorded on the Serious Adverse Event Report Form. The investigator must assess and record the relationship of each SAE to each specific study drug (if there is more than one study drug), complete the SAE Report Form in English, and send the completed, signed form within 15 days to Novartis Safety Desk.

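### The hospitalisation bullet of the SAE definition is literally inverted, so some unplanned admissions could be left out of SAE reporting

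*Protocol*

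**What the plan says.** Protocol section 7.4.3 defines an SAE in five bullets. The first three cover fatal or life-threatening events, lasting or significant disability, and congenital anomalies. The fourth is "In a medical emergency, i.e. when the subject is at risk or needs medical or surgical intervention to prevent the consequences described above". The fifth is the only one on hospitalisation: "Admission is not considered a serious adverse event if hospitalization or extension of existing hospitalization is required, such as". Four items follow it:

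- "Common treatments not related to disease worsening"
- "Selective and pre-planned treatment of existing disease that is not related to the indications of this trial", where that disease has not worsened since the study drug was started
- "Emergency outpatient treatment that does not fall within the definition of serious adverse events described above and does not result in hospitalization"
- an item on social reasons and general deterioration, whose wording is garbled

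The same section requires every adverse event to go on the CRF with a flag for whether it is serious. It also requires the action taken to be recorded, and one of the listed actions is "Subject Admission / Extension of the period of stay for the subject".

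Section 7.5 sends "every SAE, regardless of suspected causality, occurring after the patient signs the informed consent" to the safety desk within 15 days of the site learning of it. This duty continues until 4 weeks after study treatment stops.

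**The concern.** A list of seriousness criteria should tell a site which events to report. On hospitalisation this one says the reverse of what its own sub-items imply. A site that follows the sentence as printed would not classify an unplanned admission as serious unless another bullet applied. A site that infers the intended rule would.

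The trial is multi-centre (section 1.2), so both readings can be in use at once. What is at stake is the completeness of expedited safety reporting in patients aged 50 to 90, and whether SAE counts mean the same thing at every centre. The primary outcome, the sample size and the main analysis are not touched.

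**Working it through.** No figure in the protocol bears on this point, so the check is of the text.

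**Step 1. Does any bullet make hospitalisation serious?**

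| Bullet in section 7.4.3 | Does it catch an unplanned admission? |
| --- | --- |
| 1. Fatal or life-threatening | Only if the event is that severe |
| 2. Disability | Only if function is lastingly or significantly impaired |
| 3. Congenital anomaly | No |
| 4. Medical emergency | Some: where the subject is at risk, or intervention is needed to prevent the outcomes in bullets 1 to 3 |
| 5. Hospitalisation | As printed, it says such an admission is not serious |

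Bullet 4 refers back to the consequences above it, and hospitalisation comes below it. It therefore does not supply the missing criterion. An unplanned admission for a non-emergency event that is neither life-threatening nor disabling meets none of the five.

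**Step 2. Is bullet 5 consistent with its own items?**

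- Items 1 and 2 (routine treatment; elective, pre-planned treatment) need exempting only if admission otherwise counts as serious.
- Item 3 exempts emergency outpatient care on condition that it "does not fall within the definition of serious adverse events described above and does not result in hospitalization". That condition implies that care which does end in admission is treated differently. The lead-in sentence says otherwise.
- Item 4 appears to be meant as an exemption for social admissions. It also names general deterioration and speaks of cases without a short hospital stay, so its scope cannot be read with confidence.

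The items describe exceptions to a rule that is not written, and the sentence introducing them states the opposite rule. The sentence is complete, with no sign of redaction or lost text.

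**Step 3. What depends on the definition?**

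Two things: the seriousness flag on each adverse event (section 7.4.3) and the 15-day report (section 7.5). If the flag is negative, nothing else in the protocol triggers the report.

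**Step 4. What survives a literal reading?**

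During treatment the event is still recorded as an adverse event, and admission or a longer stay can be recorded as the action taken. It can be found and reclassified later, although the protocol describes no step for doing so and the 15 days would have passed.

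After treatment this safeguard is weaker. Adverse events are sought by questioning at visits, and the last scheduled visit is week 24 or early termination (section 7, Table 1). The SAE duty runs 4 weeks beyond the end of treatment. An admission in that period that is not called an SAE has no scheduled visit at which it would be picked up.

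**Step 5. Can the effect be sized?**

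No. That would need an unplanned-admission rate and the share of those admissions that meet bullets 1 to 4. The protocol gives neither. Applying an assumed rate to the planned 300 patients would count every admission as excluded, including those that qualify under another bullet. It would be at most an upper bound on an invented input, so no figure is given.

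**The case against.** The best case for the plan has four parts.

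- **The intent is recoverable.** The sub-items show that the author meant hospitalisation to be serious with exceptions. Other passages of the protocol are similarly garbled, which points to a language fault rather than a chosen rule. This stands as an explanation. It does not remove the problem, because each site applies the text in front of it.
- **The medical-emergency bullet catches many admissions.** This stands in part. Many acute admissions could qualify under it, so the gap is smaller than the inverted sentence suggests, but it is not closed.
- **Events are not lost.** This stands for the treatment period. What is exposed is the seriousness flag and the timely report, not the capture of the event.
- **No SAE analysis is affected.** A reader might infer that the inverted bullet makes the SAE comparison between the two groups wrong. The documents do not support that. Section 4.3 lists adverse events among the secondary parameters in the two groups, and the section on analysis of the secondary objective describes SAE monitoring, but no SAE test or rate is specified. Both groups receive the same drug under the same definition. A difference in misclassification between groups is possible but not shown.

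A reader might also infer that hospital admissions in general would go unreported. That is too strong for the reasons in the second and third parts.

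**Conclusion.** The point holds in a limited form, and the text must be corrected. The hospitalisation bullet in section 7.4.3 is inverted as written and contradicts its own exemptions, and no other bullet makes hospitalisation a criterion. Unplanned admissions that meet no other criterion could be left out of SAE reporting, or be classified differently between centres.

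The textual finding rests on no numerical assumption. The consequence rests on at least some centres applying the sentence literally, which the documents cannot settle. The number of patients affected cannot be derived. The importance of the point comes from expedited safety reporting, not from any effect on the efficacy result.

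**What to change.** 1. Reconcile the bullet with its exemptions: state that an event requiring hospitalisation, or prolonging an existing hospitalisation, is serious, and give the listed cases as exceptions.
2. Reword the third item. Outpatient care that does not lead to admission is not an exception to hospitalisation. It belongs in a separate sentence saying that such care does not by itself make an event serious.
3. Reword the fourth item so that its scope is clear, in particular whether admission for general deterioration is meant to be exempt. Keeping all four items verbatim under a corrected lead-in would not be enough.
4. List all adverse events whose recorded action was admission or an extended stay, and check their seriousness flag against the corrected definition. The CRF listing may miss the 4 weeks after treatment, so ask sites directly about admissions in that period. Parts of the protocol are in the past tense; if the trial has already been conducted, this re-screen still applies.

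The cost is one corrected bullet list, approved by the institutional review boards as the protocol requires for changes, and a short listing review. No change to the sample size, visits or efficacy analysis is needed.
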